#### Secondary analyses

The secondary outcomes examined will include mindfulness and perceptions of social work environment. We anticipate conducting the following analyses:*Effect of the intervention on mindfulness*: We will examine the effect of the intervention on mindfulness score using the same model as the primary analysis with MAAS score as the outcome.*Effect of intervention on perceptions of social work environment*: We will examine the effect of the intervention on perceptions of social work environment (social support and network conflict) using the same model as the primary analysis with the 4 VAS.*Analysis of mindfulness and perceptions of social work environments as mediators of stress reduction*: We will conduct analyses of the mediation effect of mindfulness (MAAS measures) and perceptions of social work environments (workplace social support and conflict VAS measures) on the intervention, estimating the direct and indirect causal effects using the approach of Imai [73].*Effect of training participation on stress:* Training participation will be examined using two measures: number of trainings completed as measured by access logs for viewing training videos and self-report mean number of days per week on which mindfulness was practiced. The effects of level of participation will be examined using repeated measures mixed effects models, with the effect of participation level assessed by interaction terms between level of participation and follow-up time. The models will include level of participation as a covariate, fixed effect for time (3 levels; baseline, post intervention and follow up), site, time–by-level-of-participation interaction and a random intercept for participant.*Effect of online Toolkit*: A secondary aim of this study is to determine the extent to which an online Toolkit for reducing occupational stress in call centers improves call center climate four months post implementation of the Toolkit. We will use a multi-level model to examine the effects of implementation of the toolkit (as measured through the manager survey) on mean call center stress levels and call center climate, as measured by workplace support and conflict measures.

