### Project aims

The objective of this study is to develop and test the effectiveness of an evidence-based, multi-level intervention program designed to reduce stress in 9-1-1 TCs. The project’s primary aim is to:develop, implement, and test the effectiveness of an individual-level online mindfulness training to reduce stress in 9-1-1 telecommunicators.

The secondary aims are to:develop and test the effectiveness of an organizational-level online worksite stress reduction toolkit utilized by 9-1-1 TC managers that is designed to reduce or minimize sources of stress in the 9-1-1 call center environment.test if the multi-level intervention program will lead to increases in TCs’ positive perceptions of the call center social work environment.test if participation in the mindfulness training increases mindfulness.test if increases in TC’s positive perceptions of the call center social work environment and increases in mindfulness serve as mediators of stress reduction in 9-1-1 TCs.

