### Conceptual framework

Borrowing from the literature on occupational stress, individual stress, and coping response we developed a conceptual framework that describes how this multilevel intervention is expected to effect stress in 9-1-1 telecommunicators (Fig. 1). At the individual level, mindfulness training is hypothesized to increase an individual’s ability to regulate their emotional response to stressors, whereas the call center manager-directed organizational level intervention is hypothesized to reduce worksite stressors and increase perceived social support by implementation of targeted strategies and worksite policies.

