### Randomization

Respondents from each enrolled call center who are eligible, have provided their informed consent, and have completed the baseline survey, will be randomized into either the mindfulness training group or wait-list control group.

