#### Online stress reduction toolkit

Following the intervention group participants’ completion of the mindfulness training and completion of the second survey, managers of all participating call centers will be provided with a link to access the Toolkit and are asked to share the link with other administrative personnel at their call center who may be in a position to implement any of the suggested activities. Managers will have access to the Toolkit for 3 months and will receive bi-monthly emails encouraging them to use the Toolkit content and directing them to specific modules of the Toolkit. After 3 months access to the Toolkit, all participants complete the third survey.

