#### Mediating variables

Data regarding the following variables hypothesized to serve as mediators to the main outcome will be collected.*Social Support***:** Perceptions regarding social support (at work with coworkers and at home with family and friends), assessed by two separate visual analogue scales (VAS). Prior research has established the reliability and concurrent validity of these measures in another first responder sample [58].*Network Conflict*: The degree of conflict experienced at home and at work, assessed by two separate VAS. Prior research has established the reliability and concurrent validity of these measures in another first responder sample [58].*Mindfulness*: The Mindful Attention Awareness Scale (MAAS) will assess attentional sensitivity to psychological, somatic, and environmental cues [59]. Prior research has documented internal consistency reliability estimates were of good quality (α ranged = .89–.93) and test–retest reliability correlations between the repeated MAAS measures were all of medium-to-large magnitude and statistically significant [60]. The Five Facet Mindfulness Questionnaire (FFMQ) will assess five factors associated with mindfulness. Sound psychometric properties for the FFMQ have been consistently observed, including construct validity for the global FFMQ score, as well as adequate to strong internal consistency for the global score and subscales (α = .67-.93) [61–68]. The five factor hierarchical structure has been confirmed in samples of mediators and non-mediators [61, 68].

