#### Primary analyses

To examine the primary hypothesis we will use repeated measures mixed effects models, with differences assessed by interaction terms between randomization group and follow-up time. The models will include fixed effects for group (2 levels) and time (3 levels; baseline, post intervention and follow up), site, time–by-treatment interaction, and an interaction term between the implementation of the center wide toolkit and the third time point, with a random intercept for participant. Differences between groups will be assessed using the time-by-treatment interaction term.

The primary outcome variable will be the C-SOSI symptoms of stress scale. Hypotheses will be conducted at the 0.05 level of significance without adjustment for multiple comparisons, with group assigned according to intent-to-treat.

The effects of possible differential drop-out rates between the two groups will be assessed using sensitivity analyses under the assumption that data is not missing at random. Multiple imputation will be used to impute missing values for the outcome variable under varying levels of bias, and the resulting association between level of bias and differences between the groups estimated.

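### The arm-by-time contrast named for the social-work-environment aim tests mindfulness training alone, not the multi-level program, and two of its four scales measure home life

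*Protocol article*

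**What the plan says.** - **Aim** (Project aims): to "test if the multi-level intervention program will lead to increases in" telecommunicators' favorable perceptions of the social environment at work. The exposure is the whole program, not one component.
- **Expected mechanism** (Conceptual framework): "the call center manager-directed organizational level intervention is hypothesized to reduce worksite stressors and increase perceived social support". Mindfulness training is described there as acting on how the individual regulates emotional responses.
- **Allocation** (Randomization): "Respondents from each enrolled call center who are eligible", consenting and with a completed baseline survey, are randomized as individuals.
- **Toolkit delivery** (Online stress reduction toolkit): after the second survey, "managers of all participating call centers will be provided with a link to access the Toolkit". Study design says the same.
- **Analysis of this aim** (Secondary analyses): "using the same model as the primary analysis with the 4 VAS".
- **Inferential term** (Primary analyses): "Differences between groups will be assessed using the time-by-treatment interaction term". The model also has a term crossing toolkit implementation with the third survey.
- **Scales** (Mediating variables): for support, "Perceptions regarding social support (at work with coworkers and at home with family and friends), assessed by two separate visual analogue scales". Network conflict likewise has one scale for home and one for work.
- **Mediation** (Secondary analyses): the mediators include "perceptions of social work environments (workplace social support and conflict VAS measures) on the intervention", so workplace scales only.
- **Toolkit analysis** (last item of Secondary analyses): a multi-level model relates manager-reported implementation to center stress and to climate, with climate taken from the workplace support and conflict scales.

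**The concern.** The aim is about the program, but the contrast named for it compares trained with wait-listed telecommunicators whose centers all receive the same toolkit. The component that the framework text links to better social support is the one this contrast cannot see. If the result is reported under the aim as worded, a null could be read as failure of the program when only mindfulness training was tested, and a positive result could be credited to a program whose organizational half did not contribute to it.

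The same limit applies to mediation: the randomized exposure is the training, so an indirect effect through workplace support or conflict says nothing about the toolkit.

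Separately, listing all four scales under the work-environment outcome lets a change in home support or home conflict be reported as bearing on the call center. The same section of the protocol article defines the construct more narrowly in its mediation and toolkit analyses.

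**Working it through.** **The plan's own figure.** The only sample-size figure is 65 completers per group for 80% power at an effect size of 0.5, and 160 in total after 18% loss. Taking alpha 0.05 as two-sided, a two-sample t-test needs 64 per group (63 by normal approximation), and power at 65 is 80.8%. 65 / (1 - 0.18) = 79.3, rounded up to 80 per group, or 160. The figure reproduces; nothing below depends on it.

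**What the contrast contains.** For a workplace scale, let M2 and M3 be the training effects at surveys 2 and 3, T the toolkit effect at survey 3, S any training-by-toolkit synergy, and c2, c3 the changes over time shared by both arms. Expected change from baseline:

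| | Wait-list | Training | Difference |
|---|---|---|---|
| Survey 2 (before toolkit) | c2 | c2 + M2 | M2 |
| Survey 3 (after toolkit) | c3 + T | c3 + T + M3 + S | M3 + S |

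T appears in neither difference. With no synergy the survey-3 contrast is (M + T) - T = M, whatever the size of T. The program's effect against no program would be M3 + T + S, but no arm or center is kept free of the toolkit, so randomization does not identify T.

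**What the toolkit term adds.** It multiplies an implementation indicator by a survey-3 indicator. If every center implements equally, this column is a multiple of the survey-3 column (or all zeros), and T cannot be separated from ordinary change over time. If implementation varies, the term compares centers that did more with centers that did less, which is not a randomized comparison.

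**Numerical check.** The inputs are assumed, not taken from the document: 16 centers of 10 telecommunicators, half per arm; training effect 0.3; toolkit effect 0, 0.5 or 1.0; complete data; 200 replicates; within-participant fixed-effects estimates.

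| True toolkit effect | Arm x survey 3, all centers implement | Common survey-3 change, all implement | Arm x survey 3, half implement | Toolkit x survey 3, half implement |
|---|---|---|---|---|
| 0 | 0.297 | 0.003 | 0.297 | 0.005 |
| 0.5 | 0.306 | 0.504 | 0.289 | 0.502 |
| 1.0 | 0.290 | 1.015 | 0.318 | 1.015 |

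The arm contrast stays near 0.30 throughout. The toolkit effect goes into the common survey-3 change when implementation is uniform and into the toolkit term when it varies. The clean recovery in the last column reflects an assumption that implementation is unrelated to anything else that changes the outcome.

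**Scales.** Two constructs (support, conflict) by two settings (work, home) give four scales; 2 of 4, or 50%, are home scales. The three analyses in Secondary analyses use:

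| Analysis | Scales |
|---|---|
| Intervention effect on work environment | all 4 |
| Mediation | 2 workplace |
| Toolkit effect on climate | 2 workplace |

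**The case against.** The strongest reply is that the plan does not rely on the arm contrast alone. The same model carries the toolkit-by-third-survey term, and a separate multi-level model relates implementation to workplace support and conflict. Analyzing a two-part program by component is defensible: the arm contrast for training, the implementation model for the toolkit. A reader might infer that the toolkit's effect on climate goes unexamined, or that the aim must come out null even if the program works. The document supports neither. What remains is that the contrast named for this aim is the arm contrast, that the toolkit analysis is not tied to this aim, and that both toolkit analyses are non-randomized.

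A reader might also infer that the framework rules out any effect of mindfulness on these perceptions, which would make the mediation analysis wrong. The text does not say so. The outcome is an individual's perception, which training could change, and the framework figure is not available here. Survey 2 precedes the toolkit, so its arm contrast is a valid, toolkit-free test of training on these perceptions, and testing them as mediators of training is legitimate.

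Finally, a reader might compute that four scales instead of two raise the chance of a false work-environment finding from 1 - 0.95^2 = 9.75% to 1 - 0.95^4 = 18.5%. That needs independent scales and a rule that any one significant scale confirms the aim. Neither is stated, and the plan openly declares no multiplicity adjustment. The objection to the home scales is about what they measure, not about those error rates.

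**Conclusion.** The point holds in limited form. As planned, the arm-by-time contrast estimates the effect of mindfulness training on these perceptions, plus any synergy with the toolkit. A toolkit effect common to both arms contributes exactly 0 to it. It is valid for training but cannot answer the aim as worded for the multi-level program. The toolkit's part rests on differences in implementation between centers, which are not randomized and cannot be separated from time if implementation is uniform. Half of the scales listed under the work-environment outcome measure home life, contrary to the narrower definition used twice in the same section.

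The cancellation assumes that the toolkit acts equally on trained and wait-listed telecommunicators; any difference between them is the synergy term. The primary outcome and sample size are unaffected, but the conclusion that can be drawn on a stated secondary aim changes.

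**What to change.** 1. Test this aim on workplace support and workplace conflict only, and report the two home scales as exploratory.
2. State that arm-by-time gives the randomized effect of mindfulness training on these perceptions. Base any conclusion about the toolkit or the program on the toolkit-implementation analysis already planned, labelled non-randomized.
3. State that mediation through workplace support and conflict concerns mindfulness training only, not the toolkit.

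These are wording changes and need no new data or model. The cost is that the toolkit part of the aim becomes an explicitly weaker, associational statement, which is all that a design without a toolkit-free comparison can support.

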### Description, Design & Development of Interventions

#### Individual-level mindfulness training

The online mindfulness training is composed of seven modules to be completed weekly, over a 7-week time period. Each weekly online module is expected to require participants between 20 to 30 min to complete. Each individual module consists of the following components:A short video introducing the theme for the weekA few paragraphs describing the theme and activities for the weekAn audio-guided meditative stress reduction exerciseSuggestions for brief mindfulness activities that can be performed throughout the dayA brief check-in form for participants to let study staff know how the training is goingA moderated discussion board on which participants can post questions/comments if they wish

The mindfulness training is developed by clinicians and investigators who are trained mindfulness teachers and practitioners. The training is adapted from the widely-used Mindfulness-Based Stress Reduction (MBSR) program, an evidence-based training program originally implemented as in-person training [55, 56]. For our project, the MBSR training content was modified, abbreviated, and revised to accommodate an online format and tailored to meet the constraints and needs of the 9-1-1 TC population.

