#### Online mindfulness training

During the 7-week training period, the intervention group will be contacted each week, receiving two emails: one containing the link to that week’s training module and one providing additional suggestions for incorporating that week’s stress reduction activities into daily living. Participants will be encouraged to complete the training on a designated weekday to allow approximately 7 days between each module. Participants will also be encouraged to practice the mindfulness skills introduced in the module throughout the week for approximately 10 min every day.

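### The count of trainings completed is taken from video-viewing logs, but the only video in a module is its short introduction, so the count measures introductions viewed

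*Protocol article*

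**What the plan says.** In the protocol article, Secondary analyses, the item on training participation and stress states: "Training participation will be examined using two measures". The first is "number of trainings completed as measured by access logs for viewing training videos". The second is "self-report mean number of days per week on which mindfulness was practiced". Each enters a repeated measures mixed model, "with the effect of participation level assessed by interaction terms between level of participation and follow-up time".

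The section Individual-level mindfulness training describes what is being counted: "The online mindfulness training is composed of seven modules to be completed weekly, over a 7-week time period". On length it says: "Each weekly online module is expected to require participants between 20 to 30 min to complete". It then lists six components per module: an introductory video, a short text, a guided meditation delivered as audio, suggestions for brief activities during the day, a check-in form to staff, and a moderated discussion board. Only the first is a video.

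The section Online mindfulness training adds that, apart from the weekly module, participants are encouraged to "practice the mindfulness skills introduced in the module throughout the week for approximately 10 min every day".

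**The concern.** The label and the data source do not describe the same thing. A completed training would ordinarily mean that the module, or at least its main exercise, was done. The log records only whether the introductory clip was viewed. Applied as written, a participant who views all seven clips and never plays the audio scores 7 of 7, while one who goes straight to the audio every week scores 0.

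Two uses of the measure are at stake. Any adherence figure taken from the log would be called completion when it is not. The participation analysis would also relate change in stress to a count that only partly tracks the training received. This is the only objective participation measure that the article names, since the other is self-reported.

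**Working it through.** The article gives no adherence rate, so there is no stated figure to reproduce. The check compares the sections and then works through an illustration.

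**Comparison of the sections**

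| Item | Section | Content |
|---|---|---|
| What is counted | Secondary analyses | Trainings completed, from logs of video viewing |
| Videos in a module | Individual-level mindfulness training | One, a short introduction to the theme |
| Guided exercise | Individual-level mindfulness training | Separate component, audio |
| Check-in form | Individual-level mindfulness training | In every module, not named as a participation measure |
| Modules | Individual-level mindfulness training | 7, one per week, 20 to 30 minutes each |

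No section says that the audio exercise is logged, or that it must be played before a module counts as completed. On the text, the log is therefore a count of introductory videos viewed.

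**Illustration of the effect on the slope (assumed rates)**

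For a participant given the training, let V be the number of videos viewed (0 to 7), T the number of modules in which the exercise was done, and β the true change in stress per exercise done. Assume first that the exercise is done only after the video, with probability q per module, independent of stress.

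- T given V is Binomial(V, q), so E[T | V] = qV.
- The slope on V is then qβ, and V overstates T on average by the factor 1/q.
- q = 0.8: the slope is 0.8β, 20% too low. Completion is overstated by 1/0.8 − 1 = 25%.
- q = 0.5: the slope is 0.5β, 50% too low. Completion is overstated by 1/0.5 − 1 = 100%.

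**When the exercise is also done without the video**

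Let r be the probability that the exercise is done in a module whose video was not viewed, again independent of stress.

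- E[T | V] = qV + r(7 − V) = 7r + (q − r)V, so the slope on V is (q − r)β. Setting r = 0 returns the case above.
- Mean logged count minus mean true count = (1 − q)·mean(V) − r·(7 − mean(V)).

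The last expression can take either sign, so logged completion may be too high or too low. If skipping the video or the exercise depends on stress or motivation, the independence assumption fails and the bias in the slope need not be simple attenuation. The article gives no value for q, r or mean(V), so none of these results is an estimate for this trial.

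**The case against.** The strongest case against the point has five parts.

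- *The plan already measures practice.* The second measure, days of practice per week, would reveal someone who watches but does not practise. This stands in part. However, the article treats daily practice as an activity additional to the weekly module. Practice days are self-reported and do not show whether a given module's guided exercise was done.
- *Log details belong in the full protocol or analysis plan.* This stands for matters such as which log event counts as viewing. It does not remove the point, because the article itself states both the measure and its data source, and the two do not match the module it describes. If training videos was meant more broadly than the one clip listed, the sponsor should say so.
- *A video view is a reasonable proxy for engagement.* It is, provided that it is reported as a video view and not as completion.
- *Other components may help too.* The illustration assigns all benefit to the audio exercise. If the text and daily activities contribute, qβ is not the right attenuation. This stands and is one reason why the figures are illustrative only.
- *The analysis is peripheral.* It is one of several anticipated secondary analyses, and the effect of participation level is not listed under Project aims. This stands and limits the severity.

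A reader might infer that reported adherence will be overstated and the participation effect diluted, so that a null trial could be misread as failure of the training. The document does not support that. Once exercise without video is allowed, the direction of the error is unknown. Misreading a null primary result would also require the practice-days measure to be ignored.

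**Conclusion.** The point holds in a limited form. The definition is stated but badly fixed: it calls a count of introductory videos a count of completed trainings, and it can misclassify participants either way. The consequence is confined to adherence reporting and to one of two exposure measures in a secondary analysis. The primary comparison is made "with group assigned according to intent-to-treat" and does not use this variable.

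The net bias cannot be sized or signed from the document. The 20% to 50% understatement of the per-module slope holds only if exercises follow a viewed video, with an assumed q between 0.8 and 0.5, independently of stress, and if the exercise carries the effect. Severity: minor.

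**What to change.** In Secondary analyses, make three changes to the participation item:

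1. Report the existing log count under the name *module videos viewed*.
2. Base the count of modules completed on access to that week's audio exercise. Report check-in submission separately as supporting evidence. If audio access is not logged, use check-in submission as the completion marker and name it as such. The two should not be joined by an either-or rule, because someone who submits seven check-ins and never plays the audio would again score 7 of 7.
3. Keep self-reported practice days as the second measure.

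The cost is small: the training is online and the check-in form is already in every module, so the change needs some extra log work but no change to sample size or surveys. The downside is undercounting where the audio is used offline or a check-in is not submitted. Access also remains a proxy for doing the exercise, and the report should say so.

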**Methods/design:**

The study employs a randomized controlled trial design with three data collection points. The multi-part intervention includes an individual-level online mindfulness training and a call center-level organizational stress reduction toolkit. 160 TCs will be recruited from 9-1-1 call centers, complete a baseline survey at enrollment, and are randomly assigned to an intervention or a control group. Intervention group participants will start a 7-week online mindfulness training developed in-house and tailored to 9-1-1 TCs and their call center environment; control participants will be “waitlisted” and start the training after the study period ends. Following the intervention group’s completion of the mindfulness training, all participants complete a second survey. Next, the online toolkit with call-center wide stress reduction resources is made available to managers of all participating call centers. After 3 months, a third survey will be completed by all participants. The primary outcome is 9-1-1 TCs’ self-reported symptoms of stress at three time points as measured by the C-SOSI (Calgary Symptoms of Stress Inventory). Secondary outcomes will include: perceptions of social work environment (measured by metrics of social support and network conflict); mindfulness; and perceptions of social work environment and mindfulness as mediators of stress reduction.

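### The training-participation analysis reports as an effect an association that randomization does not protect, whichever participants enter the model

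*Protocol article*

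**What the plan says.** The paragraph on training participation under Secondary analyses uses two exposure measures. One is "number of trainings completed as measured by access logs for viewing training videos". The other is each participant's own report of how many days a week, on average, they practiced. Each goes into a repeated measures mixed model, "with the effect of participation level assessed by interaction terms between level of participation and follow-up time". The terms are then listed one by one. The list opens with "The models will include level of participation as a covariate"; after that come the three survey times, the call center site, the participation-by-time interaction and a random intercept for participant.

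The primary model is listed in the same way but is built on the randomization: "The models will include fixed effects for group (2 levels) and time (3 levels; baseline, post intervention and follow up), site", with a time-by-treatment interaction and groups kept as randomized. Group and group-by-time do not appear in the participation model. The Covariates section names age, gender, experience, overcommitment, overtime, job demands, technostress and acute events as possible confounders. None of them is listed in the participation model.

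On exposure, "The online mindfulness training is composed of seven modules to be completed weekly, over a 7-week time period", so the module count runs from 0 to 7. According to the abstract, "control participants will be “waitlisted” and start the training after the study period ends". The paragraph does not say whether controls are included in the participation model.

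**The concern.** How many modules someone finishes, and how often they practice, is decided by that person after randomization. A telecommunicator whose workload eases, or who is already recovering, may finish more modules and also report a larger fall in stress. The participation-by-time interaction then picks up that difference and attributes it to the training.

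The random intercept and the participation main effect do not prevent this. They absorb stable differences in stress level between people who complete much and people who complete little. The interaction compares changes over time, and a different trajectory among completers is exactly what it measures. The collected covariates might account for part of the difference, but they are not in the model.

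What is at stake is the reading of one secondary result. A dose-response could appear when the training does nothing, and the wording of the plan would present it as an effect of participation.

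**Working it through.** **The plan's own figure.** The article gives no figure for the participation analysis. Its sample size for the primary comparison supplies the n used below. For a two-sample t-test with effect size 0.5, two-sided 5% (sidedness is assumed) and 80% power, the normal approximation gives 2 × (1.960 + 0.842)² / 0.5² = 62.8, so 63 per group. The noncentral t gives 64, and 65 per group has 80.8% power. Allowing 18% loss, 65 / 0.82 = 79.3, so 80 per group and 160 in total. The plan's 65 and 160 are reproduced.

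**Simulation inputs.**
- From the article: 65 with data per arm, 0 to 7 modules, no training for controls during the study.
- Assumed: each person has a standard normal trait U. In the training arm, modules M are binomial (7, p) with logit p = 0.3 + 1.5U.
- Assumed: change in stress, in SD units, is −ρU + √(1 − ρ²)e, with no training effect. ρ is the strength of the link between the trait behind completion and spontaneous improvement. The documents give no value, so a range is shown.
- Simplification: one change score per person instead of three time points; 4,000 replicates per setting.

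**Results.** Apparent effect of 7 versus 0 modules in SD units, with the share of p-values below 0.05:

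| ρ | Controls at dose 0 | Training arm only | Randomized group contrast |
|---|---|---|---|
| 0 | −0.01; 5.5% | −0.02; 5.4% | 0.00; 5.4% |
| 0.1 | −0.10; 7% | −0.27; 11% | 0.01; 4.9% |
| 0.2 | −0.20; 13% | −0.54; 27% | 0.00; 5.6% |
| 0.3 | −0.32; 25% | −0.81; 53% | −0.01; 4.8% |
| 0.4 | −0.41; 39% | −1.07; 79% | 0.00; 5.4% |

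With group used as an instrument for dose, the estimate stays within 0.02 SD of zero at every ρ.

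**Analytic check.** Within the training arm the expected slope is −ρ·cov(M,U)/var(M). Under the assumed module distribution, mean M = 3.87, var(M) = 4.76 and cov(M,U) = 1.84. At ρ = 0.2 the effect of seven modules is −7 × 0.2 × 1.84 / 4.76 = −0.54. Adding an equal number of controls at zero multiplies this by var(M) / (var(M) + mean(M)²/2) = 4.76 / (4.76 + 7.49) = 0.39, which gives −0.21. Both agree with the table. Controls dilute the bias but do not cause it.

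**In points.** The article equates about 15 C-SOSI points with an effect size of 0.4 to 0.5, which implies an SD of 15/0.5 = 30 to 15/0.4 = 37.5. If that SD applies to change, the bias at ρ = 0.2 is 0.20 × 30 = 6.0 to 0.20 × 37.5 = 7.5 points with controls at zero. In the training arm alone it is 0.54 × 30 = 16.2 to 0.54 × 37.5 = 20.3 points, above the 15 that the article treats as meaningful.

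**The case against.** The strongest reply is that the plan may fit this model in the training arm only. Participation is measured by logs of training videos that controls cannot yet use, and a training-arm fit would explain why group is not listed. A reader might infer from the missing group term that controls are pooled at zero with people who chose not to start. The article does not say so, and a condensed article may leave the analysis set of a secondary model to the full plan. That part of the reply stands.

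It does not remove the problem. It would also be wrong to say that dropping the group term causes the bias: in the check, bias is larger in the training arm alone. Adding group and group-by-time to a pooled model would not help either. With all controls at zero, the dose slope would then be identified only within the training arm.

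Other replies stand in part. The analysis is secondary, is introduced as anticipated, and appears neither in the project aims nor among the secondary outcomes in the abstract. A reader might suspect that it would be used to rescue a null primary result, but nothing in the article says so. Nor does it say that controls are not asked about practice days. The false-positive rates depend on an assumed correlation and module distribution, and on a change-score simplification of the planned model.

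The instrumental analysis also needs an assumption of its own. The training arm receives two emails a week, check-in forms and a discussion board, and controls know that they are waiting. Assignment could therefore affect reported stress other than through modules completed.

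**Conclusion.** The point holds in a limited form. As specified, the participation-by-time coefficient is an observational association labelled as an effect, with no collected confounder listed in the model. It is biased if completion is related to the stress trajectory, under either reading of the analysis set. For assumed ρ of 0.1 to 0.3 and no true effect, the false-positive rate is about 7% to 25% with controls at zero and 11% to 53% in the training arm only, against about 5% for the randomized contrast. The direction assumes that people who are improving complete more. If people under growing stress complete more, the bias would run the other way and hide a benefit. The existence of the bias does not depend on the simulation; its size does. The primary comparison and the sample size are not touched, so this is an inexpensive improvement to a secondary analysis.

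**What to change.** Estimate the effect of completing the training with randomized group as the instrument for modules completed, as a complier average effect or by two-stage least squares, with baseline C-SOSI and site as covariates. State the exclusion assumption that assignment changes stress only through participation, and note the emails, the discussion board and the lack of blinding as ways in which it could fail.

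If the participation-by-time model is kept, state which participants enter it, adjust for baseline C-SOSI and the variables in the Covariates section, and report the result as an exploratory association. Because the estimate is an interaction with time, the covariates need their own interactions with time; main effects alone adjust only the level. Say that adjustment may not remove the bias.

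The cost is some analysis work and a wider interval than the pooled model gives. Under the module distribution assumed above, mean completion is 3.87/7 = 0.553. The instrumental standard error for the full course is √(2/65) / 0.553 = 0.32 SD. The pooled model gives 7 / √(130 × (4.76/2 + 3.87²/4)) = 0.25 SD, so the interval is about 1.3 times as wide. No design change and no extra participants are needed.
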